## Abstract

**Introduction:**

Human reproduction is tightly regulated by circadian and metabolic signals. However, the extent to which alterations in these systems affect fertility, especially in females with overweight or obesity who are at increased risk of infertility, remains poorly understood. This study, nested within the Healthy Early Life Moments in Singapore (HELMS) integrated lifestyle intervention program, aims to: (i) examine the associations between changes in circadian behavior and metabolic health indicators over a 3-month period and subsequent reproductive outcomes during a year of conception attempts, (ii) identify risk factors associated with these changes, and (iii) elucidate the biological mechanisms underpinning these relationships in females attempting to conceive.

**Methods:**

This prospective observational cohort study will enroll 283 females with a BMI of 25–40 kg/m² participating in the HELMS program at KK Women’s and Children’s Hospital, Singapore. Participants will be followed for one year as they attempt to conceive. At baseline and at the 3-month mark, circadian behavior will be assessed using validated questionnaires, tracking diaries, and digital wearables. Metabolic health will be evaluated through anthropometry, body fat composition, a metabolic syndrome score, and an insulin resistance index. Blood samples will be collected to analyze metabolic biomarkers and gene expression levels. We will use modified Poisson regression models to examine associations with the clinical pregnancy rate (primary outcome) and discrete-time proportional hazards models to estimate associations with fecundability (secondary outcome) within one year of conception attempts.

**Discussion:**

This study is pivotal for identifying potential novel modifiable risk factors to address low fertility rates. Insights from this research will generate hypotheses for interventions designed to enhance preconception care. By screening and managing circadian behaviors and metabolic profiles among females with overweight and obesity, these strategies may benefit those experiencing unexplained infertility. Ultimately, this approach could foster a shift towards a more holistic and patient-centered model of reproductive healthcare.

## Background

Singapore has grappled with a persistently low total fertility rate of 1.1 since 2018, which dropped to 0.97 in 2024 [1]. Despite comprehensive pronatalist policies, this rate remains one of the lowest globally, akin to many developed countries in the region [2]. This situation is complicated by biological factors, notably the sensitivity of the hypothalamic-pituitary-gonadal axis, which tightly regulates human reproduction, to circadian and metabolic cues [3]. While social factors are influential, the persistently low fertility rates in Singapore may also be partly due to increasing disrupted circadian rhythms and escalating obesity rates, stemming from unhealthy and erratic lifestyles among the population [4, 5]. This notion is supported by reviews consistently demonstrating lower pregnancy rates among shift workers and delayed pregnancies in females with excessive weight [6, 7]. Notably, overweight and obesity are increasingly common at preconception and are associated with reduced fecundability even in the absence of diagnosed infertility [8].

Besides shift work, other environmental disruptors of circadian rhythms, such as improper meal timing, sleep deprivation, and irregular sleep-wake patterns, have been associated with reduced fertility, potentially through suppression of circadian clock gene expression [3]. However, beyond sleep disturbances, the effects of unhealthy practices related to chrononutrition and chronobiology, including metabolic jet lag (a discrepancy in eating times between workdays and rest days), social jet lag (a discrepancy in sleep times between workdays and rest days), extended eating windows, and late-night eating on fertility, have not been thoroughly investigated, despite their prevalence in modern societies [9, 10]. Whether these behaviors translate into measurable metabolic perturbations relevant to reproductive outcomes in the preconception period remains unclear, and human preconception data integrating time-resolved circadian behaviors, metabolic biomarkers, and subsequent reproductive outcomes are limited.

A recent meta-analysis of randomized controlled trials revealed that while successful weight loss increased the chances of pregnancy in females with overweight or obesity, the highest weight loss did not necessarily correspond with the highest pregnancy and live birth rates [11]. Additionally, our prior study reported that females with high body mass index (BMI ≥ 23 kg/m^2^) who exhibited low insulin resistance or absence of metabolic syndrome had shorter time-to-pregnancy intervals compared with their metabolically unhealthier counterparts [12]. These findings indicate that females with overweight or obesity are a metabolically heterogeneous group, and that reproductive potential may be more closely linked to metabolic health status than to body weight per se. While animal models have provided supportive evidence for the role of metabolic hormones in correcting sterility in homozygous obese female mice [13], a lack of corresponding human data hampers the development of targeted fertility-enhancement strategies. Currently, clinical approaches predominantly focus on managing weight and BMI [11].

Taken together, the impact of circadian and metabolic disruptions prior to conception on female reproductive outcomes, especially among those with overweight or obesity who face a higher risk of infertility, remains poorly understood. The mechanisms and extent of these effects on fertility have not been adequately explored, constraining the development and implementation of effective interventions and educational programs in both public and clinical settings. This gap underscores a significant unmet need in preconception care and forms the primary motivation for this study. Therefore, our goals are to identify specific modifiable circadian behavior and metabolic health indicators that potentially contribute to reproductive outcomes, which can be targeted for intervention to improve reproductive health in preconception females. By additionally exploring changes in circadian- and metabolism-related gene expression, this study seeks to provide biological context linking circadian behavioral and metabolic changes to reproductive outcomes. Figure 1 illustrates the conceptual framework of the present study.

**Fig. 1 Fig1:**
[figure not shown]
Study conceptual framework. The diagram illustrates the relationships between circadian behavior and metabolic health indicator changes, and subsequent reproductive outcomes, specifically pregnancy rate and fecundability, among preconception females with overweight and obesity. It also investigates associated risk factors based on socio-demographics and general lifestyles, and delves into the underlying molecular mechanisms through gene expression analysis

### Objectives

The overall objective of this study is to determine how changes in circadian behavior and metabolic health indicators are associated with reproductive health outcomes in females with overweight or obesity who are attempting to conceive within the HELMS program. Additionally, this study seeks to identify associated risk factors and explore the biological mechanisms underlying these relationships. We hypothesize that desirable changes in circadian behavior and metabolic health indicators are associated with favorable reproductive outcomes in preconception females with overweight and obesity. These changes are expected to correlate with specific characteristics of the females and are accompanied by concurrent alterations in the expression levels of specific genes, particularly those related to circadian rhythms, metabolism, and fertility. The specific objectives are:

To examine the association between changes in circadian behavior (meal and sleep timing) and metabolic health indicators (BMI, body fat composition, and metabolic biomarkers) over a 3-month period, and subsequent reproductive outcomes (clinical pregnancy rate and fecundability) within one-year of conception attempts among preconception females with overweight or obesity.To identify baseline socio-demographic and lifestyle factors associated with changes in circadian behavior and metabolic health indicators among these females.To explore the relationship between concurrent changes in circadian behavior and metabolic health indicators, and gene expression levels.

## Methods/design

### Study design and setting

We conduct a prospective observational preconception cohort study, named Temporality, Eating and Metabolic health during PreconceptiOn (TEMPO), among females with overweight or obesity who are attempting to conceive over a 12-month period from recruitment. TEMPO is nested within the ongoing Healthy Early Life Moments in Singapore (HELMS) integrated lifestyle intervention program, which was initiated in March 2022 at KK Women’s and Children’s Hospital, Singapore [14]. TEMPO was introduced into HELMS in March 2024.

### Participants and recruitment

Participants who meet eligibility criteria are recruited from the HELMS starting from the baseline visit, with a one-year follow-up period. Recruitment is expected to be completed by December 2025, and follow-up data collection by January 2027.

### Inclusion criteria

Females aged 21–40 years.BMI between 25 and 40 kg/m^2^ (those with BMI > 40 kg/m^2^ are excluded due to special clinical needs and potential bariatric surgery considerations).Of Chinese, Malay, Indian ethnicity, or any combination thereof.Planning to conceive within one year.Ability to understand English.Access a mobile app on iOS or Android platform.Provision of written, informed consent.

### Exclusion criteria

Currently pregnant.Known type 1 or type 2 diabetes.Use of any anticonvulsant medication within the past month.Use of any oral steroid within the past month.Use of any oral, injectable, patch or implanted contraception or an intrauterine contraceptive device in situ within the past month.Use of any fertility medication other than Clomid/ Letrozole (Femara) within the past month.Use of HIV or Hepatitis B or C medications within the past month.History of gynecological masses or tumors.

### Patient and public involvement

The development of the current TEMPO study protocol was informed by feedback from participants in the ongoing HELMS study. This feedback process allowed us to ascertain participant preferences that significantly influenced the refinement of our study workflow. Specifically, participants’ willingness to respond additional questionnaires, attend an additional 3-month physical visit, undergo further blood collections, and their preferences for visit timings have critically shaped both the design and assessment strategies of this study.

### HELMS integrated lifestyle intervention

HELMS is conceptualized as a new model-of-care that employs an early life course approach through a mobile health platform to transform maternal and child health in Singapore [15]. The HELMS study is designed as an implementation trial to assess the efficacy of this innovative model in optimizing the metabolic and mental health of females with overweight or obesity throughout the preconception, pregnancy, and postpartum periods. Details of the HELMS protocol have been published elsewhere [14]. In brief, the intervention components specific to the preconception phase, which are similarly experienced by all TEMPO participants, include the following: After initial baseline assessments, each participant consults a doctor who provides in-person consultations and prescribes micronutrient supplements. The HELMS mobile app is introduced to provide educational materials on self-care, sexual health, and healthy lifestyles. Equipped with feedback and goal-setting functions, the app utilizes participants’ data inputs to generate reports and recommendations, guiding them towards a healthier behavior. Weekly motivational nudges are sent via the app throughout one year of conception attempts to offer anticipatory guidance in preconception care and encourage healthy lifestyle habits.

### Study procedure

Figure 2 illustrates the study workflow. The study begins with participants providing written informed consent at the HELMS baseline visit. During this visit, participants complete questionnaires assessing socio-demographics, medical history, and lifestyle factors. Socio-demographic data include age, ethnicity, education, household income, and employment status. Medical histories focus on chronic diseases and obstetric history, while lifestyle factors cover alcohol intake, smoking status, physical activity (International Physical Activity Questionnaire) [16], nutritional behaviors (Food Frequency Questionnaire or Diet Screener, and 6P Nutrition Tool) [17–19], emotional health (Edinburgh Postnatal Depression Scale) [20], and sleep quality (Pittsburgh Sleep Quality Index) [21]. Clinical measurements such as blood pressure, height, weight, body fat composition, and waist circumference are taken using standardized equipment and are recorded in duplicate. Participants undergo a standard 75 g oral glucose tolerance test and provide blood samples, which will be analyzed for glucose, insulin, and lipid profiles within two hours of collection. Additional blood samples are collected for gene expression analysis and storage for future analyses.

**Fig. 2 Fig2:**
[figure not shown]
Study workflow and measurements. Baseline, 3-month, and 6-month visits include the administration of questionnaires or diaries, physical measurements, and blood tests. Participants track their frequency of sexual intercourse, menstrual periods, sleep, and activity using a mobile application and digital wearable while trying to conceive. The 9-month visit consists of a phone call where research staff check participants’ pregnancy status and conception attempts if no update received. Throughout the follow-up period, participants with a positive urinary pregnancy test are invited to undergo a dating scan at 6–10 gestation weeks to confirm pregnancies, with outcomes retrieved from medical records. Participants who do not conceive by 12-month will be invited to attend a medical review and referred for fertility medical treatment before withdrawal from the study

At the same visit, each participant receives a digital wearable ‘Oura Ring’ (Oura Health Oy, Finland) for continuous monitoring of sleep and activity. The participants are guided on how to use the HELMS mobile app to track dietary intake, sleep-wake patterns, sexual activity, and menstrual cycles, with a paper diary available as an alternative. Participants are instructed to promptly report any positive pregnancy tests after the baseline visit to schedule an ultrasound confirmation. Physical follow-up visits, which include the same assessments as at baseline, are scheduled at 3-month and 6-month intervals if conception has not occurred, during which conception attempts and family planning decisions are monitored. At 9-month, research staff conduct a follow-up phone call to check on conception attempts and pregnancy status. By 12-month, non-pregnant participants undergo a final health review and are referred for fertility treatment if needed.

Partner assessments are conducted once at the baseline visit during the preconception period to collect socio-demographics, medical history, chrononutrition profile, weight, height, and body fat composition; semen analysis results are retrieved from medical records, if available. Detailed data collection is summarized in Table 1.

**Table 1 Tab1:** Data collection

	Baseline	3-month	6-month	9-month	12-month
Informed consent	√				
Eligibility criteria	√				
Background characteristics^a^					
Socio-demographics	√				
Medical history	√				
Lifestyles					
Alcohol intake and cigarette smoking	√	√ ^b^	√		
Physical activity	√	√ ^b^	√		
Dietary pattern	√	√ ^b^	√		
Emotional health	√	√ ^b^	√		
Sleep quality	√	√ ^b^	√		
Circadian behavior					
Chrononutrition profile^a^	√	√ ^b^	√ ^b^		
Chronotype	√				
Food and sleep diary	√				
Digital wearable (sleep & activity)	√ ^b^ (throughout the period of trying to conceive)				
Metabolic health					
Blood pressure	√	√ ^b^	√		
Height*	√	√ ^b^	√		
Weight and body composition^a^	√	√ ^b^	√		
Fasting plasma glucose	√	√ ^b^	√		
2-hour plasma glucose	√				
Fasting serum insulin	√	√ ^b^	√		
Fasting serum lipid panel	√	√ ^b^	√		
Reproductive health					
Serum Anti-Müllerian Hormone	√				
Pregnancy status and attempts	√	√	√	√	√
Menstrual cycle & sex frequency	√	√	√	√	√
Ultrasound dating scan (if pregnant)	√ (6–10 gestation weeks)				
Gene expression analysis	√ ^b^	√ ^b^			

^a^Measurements which are similarly performed on male partners

^b^The additional measurements introduced in the TEMPO study, which complement the existing measurements in HELMS

### Circadian behavior assessment

Circadian behavior is assessed using the Chrononutrition Profile Questionnaire [22, 23], which evaluates key variables such as metabolic jet lag, social jet lag, nocturnal eating, breakfast skipping, eating windows, and sleep duration. The Chrononutrition Profile Questionnaire, comprising 18 items, captures general patterns of chrononutrition preferences and behaviors on typical work/school days and free days. It includes questions on meal timing, frequency of meals and snacks, sleep-wake times, and the type of the largest meal intake. Desirable changes in circadian behavior are defined as reductions in metabolic and social jet lag, nocturnal eating, breakfast skipping, and eating window duration, together with shifts towards longer sleep duration, as well as earlier meal and sleep timing. Additionally, chronotype will be determined using the Morningness-Eveningness Questionnaire consists of 19 items, each rated on a 4 or 5-point numerical scale, with total scores ranging from 16 to 86; higher scores indicate a morning-type tendency [24]. The accuracy of these self-reported measures will be enhanced by cross verifying the same variables using food and sleep diaries (covering three workdays and one rest day) and data from digital wearables.

### Metabolic health assessment

BMI is calculated by dividing an individual’s weight in kilograms by the square of their height in meters. Body fat percentage and distribution are measured using the InBody 970 Body Composition Analyzer (InBody, Korea), which employs bioelectrical impedance analysis technology and direct segmental measurement. A metabolic score is derived based on metabolic syndrome criteria, awarding one point for each of the following conditions: (i) waist circumference ≥ 80 cm; (ii) triglyceride ≥ 1.7 mmol/L; (iii) high density lipoprotein-cholesterol < 1.3 mmol/L; (iv) fasting glucose ≥ 5.6 mmol/L; and (v) blood pressure ≥ 130/85 mmHg, or on treatment [25]. Insulin resistance is calculated based on the updated homeostasis model assessment of insulin resistance (HOMA2-IR) index, accessible via the HOMA2 calculator online at http://www.dtu.ox.ac.uk/homacalculator/ [26]. Desirable changes in metabolic health are defined as reductions in BMI, body fat percentage, visceral fat area, metabolic syndrome score, and insulin resistance.

### Gene expression analysis

Peripheral blood samples for gene expression analysis are collected in Tempus blood ribonucleic acid (RNA) tubes, from which total RNA will be extracted. RNA sequencing will be conducted on a selected subset of samples to identify candidate genes. Subsequently, reverse transcription-quantitative real-time polymerase chain reaction will be performed on all other samples to validate these findings. To quantify changes in gene expression, the 2 − ΔΔCt method will be used, comparing gene expression levels at baseline with those at the 3-month follow-up.

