To examine the associations of circadian behavior and metabolic health indicator changes with fecundability, we will use discrete-time proportional hazards models. These models analyze time-to-pregnancy on a discrete scale (number of menstrual cycles-at-risk during active pregnancy attempts), to estimate the hazard ratio of fecundability, termed as the fecundability ratio, along with a 95% confidence interval [31]. Adjustments for potential covariates will be made, similar to those used in the above Poisson regression models [6, 12, 29, 30]. Unlike the hazard ratio for mortality or morbidity where a ratio of < 1 is desirable, a fecundability ratio of < 1 indicates an undesirable outcome which suggests delayed pregnancy. We will account for left truncation by basing our analysis on risk sets for observed cycles at risk, considering only the cycles actively attempted during the study period. For instance, if a participant has been trying to conceive for four cycles at study entry and achieves pregnancy after seven cycles, only the cycles from the fifth to the seventh will be included in the analysis. Participants will be censored in the analysis if they do not conceive after 12 months from recruitment, start fertility treatment, cease trying to conceive, or are lost to follow-up.

To analyze the associations of socio-demographic and lifestyle factors with circadian behavior and metabolic health changes, we will employ multivariable linear regression for continuous outcomes and multinomial logistic regression for categorical outcomes, adjusting for potential covariates. For the assessment of changes in circadian behavior and metabolic health indicators with gene expression levels, we will utilize independent t-tests or Mann-Whitney U test to evaluate differences in gene expression between groups categorized by high versus low health indicators, determined by median thresholds at each time point. Additionally, correlation testing (Pearson or Spearman) will identify associations between these variables and gene expression. Corrections for multiple testing, such as Bonferroni or false discovery rate, will be applied to reduce the Type I error rate.

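### For genes with a daily rhythm, the stated gene analysis cannot separate a shift in phase from a change in expression level

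*Protocol article*

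**What the plan says.** All references are to the Protocol article.

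- *Gene expression analysis*: "Peripheral blood samples for gene expression analysis are collected in Tempus blood ribonucleic acid (RNA) tubes". The measure of change is 2-ΔΔCt, "comparing gene expression levels at baseline with those at the 3-month follow-up". Table 1 marks gene expression at baseline and 3 months only.
- *Objectives*: the third aim is to explore how concurrent changes in behavior and metabolic indicators relate to expression. The hypothesis concerns specific genes, "particularly those related to circadian rhythms, metabolism, and fertility".
- *Circadian behavior assessment*: desirable change includes "shifts towards longer sleep duration, as well as earlier meal and sleep timing". A change in timing is therefore one of the exposures.
- *Statistical analysis plan*: groups split at the median of an indicator at each time point are compared by t-test or Mann-Whitney test. In addition, "correlation testing (Pearson or Spearman) will identify associations between these variables and gene expression". A multiplicity correction is planned. No covariate is named for the gene analysis, whereas the Poisson, discrete-time hazards, linear and multinomial models are all adjusted.
- The limitations in the *Discussion* do not mention time of sampling or phase.

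**The concern.** A reading of a rhythmic gene at one time of day depends on the level of the rhythm, its amplitude and the phase at which the blood is drawn. Here the exposure may itself move the phase. Suppose a woman is bled at the same clock time at both visits but wakes earlier at 3 months. She is then sampled later in her biological day, and ΔΔCt moves even if the rhythm has kept its level and amplitude. This error is tied to the exposure, so it acts as bias rather than noise, and a multiplicity correction does not remove it. The comparisons at each visit are open to the same problem, because early and late sleepers bled at one clock time differ in phase.

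At stake is the reading of the third objective. The *Background* raises suppressed clock-gene expression as a possible path from circadian disruption to lower fertility. A phase shift could be reported as support for that path.

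**Working it through.** **The plan's own figures.** The article gives no sample size or precision for the gene analysis. Its only calculation is for the primary aim, and it reproduces: 2 × (1.960 + 0.842)² / 0.4² = 98.1, so 99 per group and 198 in total; 198 / 0.70 = 282.9, so 283. These figures do not bear on this point, except that 198 serves as n in the simulation below.

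**Model (assumed).** Let log2 expression at t hours from peak be M + A cos(2πt/24). M is the level and A is half the peak-to-trough range. For an F-fold rhythm, A = log2(F)/2. If M and A stay fixed and the sample falls d hours later in the rhythm, the reading changes by A[cos(2π(t+d)/24) − cos(2πt/24)]. Its largest absolute value is 2A sin(πd/24).

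For F = 2, 2A = 1, so the maximum is sin(πd/24):

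- d = 1: 0.131 log2 units, 2^0.131 = 1.09
- d = 2: 0.259 log2 units, 2^0.259 = 1.20
- d = 3: 0.383 log2 units, 2^0.383 = 1.30

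The documents give no amplitude, so a range follows (largest apparent fold change):

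| Assumed rhythm, peak to trough | 1 h | 2 h | 3 h |
|---|---|---|---|
| 1.5-fold | 1.05 | 1.11 | 1.17 |
| 2-fold | 1.09 | 1.20 | 1.30 |
| 4-fold | 1.20 | 1.43 | 1.70 |

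**Place on the curve.** These maxima apply on the steep part. From exactly the peak of a 2-fold rhythm, the change is 0.5 × (1 − cos 15°) = 0.017 log2 units for 1 h (about 1%) and 0.5 × (1 − cos 30°) = 0.067 for 2 h (about 5%). It has the same sign whichever way the phase moves, so a linear association largely cancels.

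**Effect on the planned correlation.** A simulation assumed no true change in level or amplitude, n = 198 and 1,000 runs per setting. Further assumptions were a sleep shift with SD 1 h that phase follows one for one, baseline phase with SD 1 h between women, draw time with SD 0.5 h at each visit, and noise with SD 0.4 log2 per sample. The table gives the share of runs in which the Pearson correlation of sleep shift with expression change had p < 0.05:

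| Rhythm | Draw at peak | 3 h from peak | 6 h from peak (steepest) |
|---|---|---|---|
| None | 4% | 5% | 6% |
| 1.5-fold | 5% | 22% | 44% |
| 2-fold | 4% | 55% | 84% |

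For the 2-fold rhythm at the steepest point, with shift SD of 0.5 or 1 h and noise SD of 0.3 or 0.6, the share ran from 17.5% to 97%. These are nominal 5% rates for one gene before any multiplicity correction. The median-split tests at each visit were not simulated in the form the plan gives.

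**Which data could supply time since waking.** Under *Study procedure*, the ring is handed out and app tracking is taught at the baseline visit, so neither is shown to cover the morning of the baseline draw. Table 1 lists the food and sleep diary at baseline only. The Chrononutrition Profile Questionnaire, which asks for usual sleep and wake times, is marked at both baseline and 3 months. It is the one stated source of wake time common to both draws.

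**The case against.** The other side has several fair points.

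- The article is condensed. A draw window and time stamps may stand in a laboratory manual. Table 1 also lists "Fasting plasma glucose" at both visits, so a morning draw is likely. This stands, and the lack of a stated draw time is not the point made here. A fixed clock time, however, does not fix time since waking, and the tests as stated adjust for neither.
- *Patient and public involvement* says of HELMS participants that "their preferences for visit timings have critically shaped both the design and assessment strategies of this study". A reader might infer that draws occur at varying clock times. The text does not say so; it may concern which visits are held. Draw-time variation unrelated to the exposure would in any case add mainly noise.
- A reader might infer that each visit yields exactly one RNA sample. This rests on a single mark in Table 1, and *Study procedure* uses the plural: "Additional blood samples are collected for gene expression analysis and storage for future analyses". Still, no serial sampling is described.
- A reader might infer that an association of earlier sleep with clock-gene change must arise, or that the third objective cannot be met. Neither is supported. The distortion is small near peak or trough, and phase may not follow wake time one for one. Many indicators, such as BMI and insulin resistance, are not shifts in sleep timing, and the aim is only to explore.
- With clock time fixed, the change in time since waking is almost the same variable as the change in wake time. Adjusting for it can remove the exposure under study. This stands and shapes the fix.

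**Conclusion.** The point holds for genes with a daily rhythm: followed as written, the analysis can report a phase shift as a change in expression level. For an assumed 2-fold rhythm, the false change is at most about 9%, 20% or 30% for a shift of 1, 2 or 3 h. Under the simulation's assumptions, the planned correlation for one such gene can be significant far more often than 5% of the time when the draw falls on the steep part of the curve. Amplitude, shift size and the link between wake time and phase are all assumptions.

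Genes without a rhythm are largely unaffected, and so are indicators unrelated to sleep timing. The primary and secondary outcomes are not touched. The matter is worth correcting because the remedy is cheap and the likely misreading, phase taken as mechanism, falls on the genes the study singles out.

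**What to change.** 1. Record, or retrieve from laboratory logs, the clock time of each RNA draw. Derive time since waking from the wake time reported that day. For samples already drawn, use the usual sleep-wake times in the Chrononutrition Profile Questionnaire, which is given at both visits, with ring data at 3 months as a check.
2. Replace the unadjusted tests with a regression of ΔΔCt on the indicator change, adjusted for the between-visit difference in draw time. For indicators other than sleep timing, also adjust for the difference in time since waking. For sleep-timing exposures, show results with and without that covariate and say that the two are nearly collinear.
3. State that results for rhythmic genes from a single time point describe expression at the sampled time and may reflect phase, so they are not read as up- or down-regulation.

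The cost is some extra data work and a more modest mechanistic conclusion for clock genes. No new samples or visits are needed. Usual wake times are a coarser measure than the wake time on the day, so for samples already drawn the adjustment will be incomplete.
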